## Abstract

Background: Although mortality rates have declined in Uganda over the last decade, maternal mortality is still high at 336 deaths per 100,000 live births, as is infant mortality at 43 deaths per 1000 live births. One in every 19 babies born in Uganda does not live to celebrate their first birthday. Many of these deaths occur within the first 28 days of life, forming the single largest category of death. Promising effects for preventing death are expected from timed and targeted counselling (ttC), an intervention package of key messages and actions that address integrated health and nutrition needs of the mothers and children, barriers and negotiation agreement, to cause sustainable behavioural change at specific timelines in the first 1000 days. Methods: The study has a quasi-experimental design in order to evaluate the implementation and effectiveness of the ttC intervention. Participants are pregnant women who have been registered by village health team (VHT) members and who live in Hoima (intervention region) or Masindi (control region) districts, who will be monitored throughout their pregnancy up to at least six weeks after delivery. A multi-stage sampling technique will be employed to select participants, the study sites being purposively chosen. Sample size is determined using the pregnancy rate from the population estimates, resulting in a total required sample of 1218 (609 each in the intervention and control group). Study instruments that will be used include the Ugandan VHT household register (in which all mothers to be studied will be registered), the ttC register (an additional tool for the study area), and a study questionnaire, to collect data at outcome level. Univariate, bivariate and multivariate analyses will be performed using SPSS to evaluate intervention effects on outcomes (e.g., relationship between pregnancy outcomes and antenatal attendance). In addition, quantitative findings will be triangulated with qualitative data, and collected through interviews and focus group discussions with participants and implementers. Discussion: The proposed study will examine the effectiveness of implementing ttC to improve maternal and child outcomes in Uganda. If ttC is effective, broader implementation of appropriate antenatal services can be advised as essential newborn care improvements. Trial registration: PACTR, PACTR202002812123868. Registered on 25 February 2020.

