### 2.5. Conceptual Framework

The proposed study aims to determine the effect of ttC on pregnancy outcomes and newborn survival in rural Uganda. Specifically, the study aims to ascertain the extent to which ttC improves uptake of timely goal-oriented ANC with a focus on the recommended visits, and to determine whether ttC contributes to the recommended hygienic birth practices. Additional aims are to establish the extent to which ttC improves essential newborn care practices during the newborn period, and to ascertain the extent to which ttC fosters positive male involvement in pregnancy and newborn care. Finally, the study aims to ascertain the relationship between ttC implementation and appropriate pregnancy weight gain by end of pregnancy and appropriate birth weight.

We expect that if the VHTs implement ttC effectively, there will be an increased uptake of ANC services in the intervention districts, including the timely attendance of goal-oriented ANC services, and the development and implementation of a birth plan. In addition, we expect essential newborn care improvements at the levels of the health facility and the community, aimed at newborn survival within the first 28 days of life, as well as improved visible male involvement in MNH care, including escorting the pregnant women for at least one ANC where couple human immunodeficiency virus (HIV) counselling and testing occurs. Ultimately, we expect these improvements to result in appropriate pregnancy outcomes and newborn survival (see Figure 1).

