### 2.8. Sample Size

The sample size is calculated using the formula for comparing differences in rates and proportions between two groups and determining the number of subjects per group^n^, using an individual binary for a two-sided significant level α and power 1-β [27]. With an anticipated effect size of 10% [δBinary = (^μ^T − ^μ^C)], α = 0.05 (two-sided), β = 0.2,^ z^1^−α^/2 = desired significance level at 95% (0.05). ^Ζ^1 − β = desired power at 80% (0.842), type of test = two-sided, and absolute risk reduction = 10%.

Since the study focuses on uptake of pregnancy services and essential newborn care, the key participants are pregnant mothers. We, therefore, estimate the pregnancy rate from each area using the 2020 population estimates per district, then turning the pregnancy rate into a percentage proportion. To estimate pregnancy rate, the focus will be on the recommended women of reproductive age within the population. Using the health care planning estimation, it is estimated that 24% of the population are women of reproductive age [28]. An estimation of number of births, abortions and foetal losses was acquired from the actual total 2019 health management and information systems [29] reports for both districts. This provided a 1107-sample size in the two districts. This will be increased by 10% to 1218 participants to cater for a non-response. Therefore, the treatment and control groups will each have 609 mothers at the end of the study.

To determine number of clusters needed (n_cluster) [27,30]: n _cluster = total number of participants in the two groups (/fixed cluster size) which is (^n^Cluster_Binary 2)/m = 1218/60, giving us 20 clusters. In order to have the same number of clusters per arm, the number of clusters will be increased to the nearest upper even number, which is 20 in this study. This means that the sample size contains 1218 pregnant mothers in 20 clusters which is the sub-county by the administrative units of Uganda [31].

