No	Variable	Description of Variable	Tool to Be Used
Dependent Variables			
1	Appropriate pregnancy weight gain at end of months pregnancy	Pregnancy weight gain of 11.5 kg to 16 kg by the end of the pregnancy	SQ
2	Newborn morbidity within the first 28 days of life	Newborn morbidity (focusing on cord infections, sepsis, asphyxia, fever, common flu and cold and diarrhea, pneumonia) within the first 28 days of life	SQ and ttCR
3	Appropriate birth weight	Appropriate birth weight of 2.5 kg or more	SQ
4	Mortality of newborns and mothers	If the mother died during pregnancy or childbirth, if the baby died either during pregnancy, childbirth or within the first 28 days of life.	SQ and ttCR
5	Overall maternal wellness	During pregnancy or newborn period, a mother does not develop sepsis, urinary tract infections, obstruction during birth or any danger signs during this period.	SQ and ttCR
Independent Variables			
1	Uptake of timely goal-oriented ANC	With a focus on the recommended four visits, the associated recommended services offered during these visits and timeliness of attendance.	VHTR, SQ and ttCR
2	Clean birthing practices	Birth attended by a skilled health provider, delivery happened in a health facility and a mama kit was used during the process.	SQ and ttCR
3	Essential newborn care practices (ENC) during the newborn period	Early initiation of breastfeeding, cord care practices, baby thermal care, sustained breastfeeding and baby WASH practices.	SQ and ttCR
4	Positive male involvement in pregnancy and newborn care	Man participates in at least one ANC, does an HIV test with the mother, available during birth, supports mother to help her rest, contributes finances for related logistics.	SQ

Notes: SQ: Study questionnaire, ttCR: ttC register, VHTR: Ugandan VHT household register.

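### Alpha, power and the 10-point effect are tied to no named outcome: the sample size rests on a pregnancy rate, and Table 4 leaves five dependent variables unranked

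*Protocol article*

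**What the plan says.** Section 2.8 of the protocol article uses a "formula for comparing differences in rates and proportions between two groups", with "α = 0.05 (two-sided), β = 0.2" and "absolute risk reduction = 10" (per cent). The rate entered is a pregnancy rate estimated for each district from population figures and health-information reports. The result is 1107, raised by 10% to 1218, or 609 per group. No outcome is attached to the 10 points.

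Table 4 lists five items under "Dependent Variables": pregnancy weight gain, newborn morbidity, birth weight, mortality of newborns and mothers, and maternal wellness. None is marked as primary. Four further items are listed as independent variables: antenatal care (ANC) uptake, clean birthing, essential newborn care and male involvement.

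Section 2.5 treats those four differently. For the first, "the study aims to ascertain the extent to which ttC improves uptake of timely goal-oriented ANC", and the other three are also set out as aims concerning the effect of ttC.

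Section 3 plans comparisons between the two areas without ranking the variables. Its examples of confounders for adjustment include attendance at a fourth ANC visit. The hypothesis in Section 1 covers two broad domains, pregnancy outcomes and newborn survival. The abstract adds: "If ttC is effective, broader implementation of appropriate antenatal services can be advised".

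**The concern.** Alpha, power and a detectable difference describe a particular test on a particular outcome. Here the only rate behind the calculation is a pregnancy rate. That bears on how many women can be recruited, but it does not say how many would have an outcome under usual care. A reader cannot tell which of the Table 4 variables has 80% power, or whether any has.

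The gap cannot be closed by assuming that the sizing covers the headline aim. Section 1 gives infant mortality in Uganda as 43 per 1000, or 4.3%. Deaths of live-born babies in the first 28 days are part of that figure, so at this rate they cannot fall by 10 points. (The mortality variable in Table 4 also counts maternal deaths and deaths in pregnancy and childbirth, so its own base rate is not given.)

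With several unranked outcomes and no deciding one, the conclusion that ttC is effective could be drawn after the results are seen, from whichever comparison looks favourable. The double role of the uptake variables adds to this. If ttC raises fourth-visit attendance, as the aims intend, adjusting for attendance can remove part of the ttC effect.

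**Working it through.** **Inputs.** Section 2.8: two-sided alpha 0.05 (z = 1.960), power 80% (z = 0.842), difference 0.10, total 1107, inflation 10%, cluster size 60. Table 4: five dependent variables and four uptake variables. Assumed, because the article does not give them: the base rate, the correlation between outcomes and the success rule.

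**1. The plan's own figure.** For two proportions, n per arm is approximately (1.960 + 0.842)² × [p₁(1 − p₁) + p₂(1 − p₂)] / 0.10². This is largest at 0.45 versus 0.55: 7.85 × 0.495 / 0.01 ≈ 389. The pooled-variance form gives 392 (784 in total), and a continuity correction gives 412 (824 in total). No base rate gives 1107 from the stated inputs. It would need an unstated design effect of at least 1107 / 784 = 1.41. With clusters of 60, the implied intracluster correlation is about 0.007 at a base rate of 0.5 (design effect 1.43; 0.43 / 59) and about 0.03 at a base rate of 0.1 (2.78; 1.78 / 59). The inflation step does reproduce: 1107 × 1.10 = 1217.7, rounded up to 1218. That 1107 cannot be rebuilt is a separate matter; here it confirms that the printed inputs do not identify the outcome.

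**2. If any one of the five at 5% counts as success (assumption).** Familywise error under independence is 1 − 0.95⁵ = 0.226. Simulation with equally correlated normal test statistics gives:

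| Pairwise correlation | Familywise error, 5 tests |
|---|---|
| 0 | 23% |
| 0.3 | 21% |
| 0.5 | 18% |
| 0.8 | 13% |

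**3. If all five must succeed (assumption).** Alpha is kept. If each test had 80% power, joint power under independence would be 0.8⁵ = 0.328, about 33%. Positive correlation would raise this, to at most 80%. If the two-domain hypothesis meant one outcome from each domain, the figure would be 0.8² = 0.64.

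**4. If the five stay co-equal under Bonferroni (0.01 each, z = 2.576).** Power per outcome falls from 80% to Φ(1.960 + 0.842 − 2.576) = Φ(0.226) ≈ 59%. Restoring 80% multiplies the sample by [(2.576 + 0.842) / (1.960 + 0.842)]² ≈ 1.49, so 1107 becomes about 1648, or about 1813 with the plan's 10%.

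**5. Roles of the uptake variables, side by side.** Section 2.5 makes the four variables things that ttC should improve. Table 4 makes them explanatory. Section 3 offers a fourth ANC visit as a confounder and, in the same parenthesis, appears to treat clean birthing as the response. The three places cannot all guide one analysis.

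**The case against.** The strongest reply is that alpha and beta in Section 2.8 are inputs to a formula. The article promises no familywise control, and it is a condensed account: testing order and multiplicity adjustment commonly sit in an analysis plan that is not shown. That stands, and the absence of a multiplicity method is not the point here. The reply does not cover the sample-size section that the article itself prints, which attaches its effect to a rate that is not an outcome.

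Three stronger readings are tempting, and the documents do not support them.

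- A reader might infer that one significant result among nine comparisons would establish effectiveness, giving 1 − 0.95⁹ = 37%. The text contains no such rule. The remark in the abstract is conditional and is not a decision criterion, and the hypothesis in Section 1 can be read as requiring both domains. Nine is the widest count, since Table 4 labels four of the variables independent. Independence is also implausible for outcomes measured in the same mothers and babies.
- A reader might take 13% to 23% as this study's false-positive risk. The range assumes that each test holds 5%. That is itself doubtful when one purposively chosen district is compared with one other.
- A reader might take the 60% in Section 1 as the baseline for four timely ANC visits. It is a national figure for completing four visits, with no timeliness condition. The same sentence puts a first visit in the first trimester at only 29%.

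**Conclusion.** The point holds in a limited form. The stated alpha, power and 10-point difference belong to no identified test: the calculation rests on a pregnancy rate, none of the five dependent variables is primary, and the four uptake variables are given conflicting roles. This follows from the text alone.

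The numerical consequence is conditional. Error would be about 13% to 23% if any of the five counted at 5%; joint power would be about 33% if all five were required, each had 80% power and they were independent. The documents choose neither rule. On either one, the pair of 5% and 80% would not describe the conclusion drawn. The point is worth correcting before the comparison is made; it does not show that the study is too small for every outcome it might name.

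**What to change.** Before the end-term comparison (February 2022 in Table 3):

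- Name one binary primary outcome in Section 2.8 and in Table 4, for which a 10-point difference is plausible.
- Restate the sample-size basis and power with that outcome's control-group rate in place of the pregnancy rate.
- Base the effectiveness conclusion on that outcome, and report the others as secondary with confidence intervals.
- Relabel the four uptake variables as outcomes of ttC, and do not adjust for them when estimating its effect.

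Completion of four ANC visits is one candidate, since the household register and the study questionnaire can supply it in both districts. At the national 60%, 60% versus 70% needs about 356 per arm before any allowance for clustering. The district rate must be checked, because enrolment takes place around the first ANC visit and requires a card or passport (Sections 2.4 and 2.9). That choice would also rest the conclusion on uptake, whereas the stated hypothesis concerns pregnancy outcomes and newborn survival. The sponsor may prefer another outcome.

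The cost is protocol wording and one recalculation. A single primary outcome needs no larger sample for multiplicity, unlike five co-equal outcomes under Bonferroni. The downsides are that the headline claim rests on one outcome and that the restated power may be less favourable.

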### 2.10. Sampling Procedure

A multi-stage sampling technique will be employed to select study participants. A total of 20 clusters of sub-counties will be selected and included in the study, based on the power calculation. Sub-counties with largest numbers of pregnant mothers registered by the VHTs will be included to ensure that the estimated study sample size is met. This will be used to increase the level of efficiency of sampling and each cluster will be considered as a sampling unit. At the beginning of the study, the team will consult the ttC registers from the VHTs in Hoima and the VHT registers from Masindi to assess the pregnancy registration per sub-county. For each sub-county, six villages will be randomly selected, with each village providing 10 households.

At the household, selection of pregnant mothers to be included in the study will be done systematically. In this probability sampling, participants will be selected from a larger population of pregnant mothers according to a random starting point and a fixed periodic interval. This periodic interval will be determined beforehand as two, which means that assuming the starting point is one as the first serial number on the VHT register, every pregnant mother with an even serial number will be selected to participate in the study, that is, 2, 4, 6, 8, etc. The sampling procedure is presented in Figure 3.

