### 2.11. Study Instruments

The study collects data from existing registries as well as through questionnaires:The Ugandan VHT household register (VHTR): This will be the entry basis into the community for both study sites. All mothers to be included in the study must have been registered by the VHT at the household level in this household register.The ttC register (ttCR): This will provide the data required for the intervention implementation analysis (process evaluation). It will also be the entry point for mothers to be included in the study and the VHTs are responsible for documentation using this register. The tool captures day-to-day visit activities between the household and the VHT.Study Questionnaire (SQ): This has been developed specifically to collect data that will be used for outcome results at the end of the intervention. An expert staff member in ttC has provided guidance that led to the revision of the tool in line with the sub-objectives. Furthermore, two researchers were asked to critically review the tool in line with the standard objectives. Their comments have been incorporated into the tool. More pre-testing of the tool will be done at the field level during the training of the enumerators.

These instruments and the variables assessed are described in more detail below.

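### Table 4 names the ttC register, kept only in Hoima by the VHTs who deliver ttC, as a source for six of nine variables, leaving the Hoima–Masindi comparison open to differential ascertainment

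*Protocol article*

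**What the plan says.** Table 4 fixes a data source for each of nine variables.

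- Newborn morbidity ends "within the first 28 days of life SQ and ttCR", and the row for deaths of newborns and mothers names the same two tools. Maternal wellness ends "any danger signs during this period. SQ and ttCR".
- Clean birthing ends "a mama kit was used during the process. SQ and ttCR" and essential newborn care ends "sustained breastfeeding and baby WASH practices. SQ and ttCR".
- ANC uptake is the only row that adds the routine register: "VHTR, SQ and ttCR".
- Weight gain, birth weight and male involvement use the SQ alone.

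The Abstract calls the ttCR "the ttC register (an additional tool for the study area". Section 2.6 has it handed out at the ttC training, and section 2.2 says that additional training took place in the intervention district. Section 2.10 draws on "the ttC registers from the VHTs in Hoima and the VHT registers from Masindi".

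Section 2.11 makes the VHTs responsible for completing the ttCR and says of its purpose: "This will provide the data required for the intervention implementation analysis (process evaluation". The same section gives the SQ the role of supplying outcome results, and describes the VHTR as the entry point at both sites. The notes to Table 3 define the end-term review as the comparison of the ttC and control areas, and the midterm review as covering ttC implementation alone.

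**The concern.** A comparison between districts is sound only if an event has the same chance of being recorded in each. Here one district has an additional record, kept repeatedly over the follow-up, and the other does not. It is kept by the people who deliver the intervention. Section 2.6 has the VHTs convened monthly to see that visits are made and entered, so the register is partly a record of their own performance.

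The direction of error depends on the variable. For illness and deaths, an extra source finds more events in Hoima and makes ttC look worse. For skilled birth, breastfeeding or cord care, entries by those promoting the practice can make ttC look better. A larger sample removes neither.

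The choice of source also conflicts with section 2.11, which separates the two tools by purpose: ttCR for process, SQ for outcomes. Three of the five dependent variables in Table 4 cross that line. The other three affected variables are labelled independent, but section 2.5 lists ANC uptake, birth practices and newborn care among the things ttC is meant to improve, so they too will be compared by district.

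**Working it through.** The plan gives no figure on this point to reproduce. The check is a count, a cross-reading and an illustration.

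**1. Count of tools in Table 4.** SQ: 9 of 9. ttCR: 6 of 9 (3 of 5 dependent, 3 of 4 independent). VHTR: 1 of 9.

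**2. Sources by district**, taking the ttCR as Hoima-only:

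| Variable | Hoima | Masindi |
|---|---|---|
| Newborn morbidity | SQ + ttCR | SQ |
| Mortality, newborn and mother | SQ + ttCR | SQ |
| Maternal wellness | SQ + ttCR | SQ |
| Clean birthing | SQ + ttCR | SQ |
| Essential newborn care | SQ + ttCR | SQ |
| ANC uptake | VHTR + SQ + ttCR | VHTR + SQ |
| Weight gain, birth weight, male involvement | SQ | SQ |

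No sentence states outright that Masindi has no ttCR. It is an inference, but the Abstract and sections 2.2, 2.6 and 2.10 all point the same way.

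**3. Illustration of size.** Assumptions not found in the article: true risk p is equal in both districts; the SQ captures a fraction s of events; the ttCR, in Hoima only, picks up a fraction r of those the SQ misses; an event counts if either source records it.

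- Observed in Masindi: p × s
- Observed in Hoima: p × (s + (1 − s) × r)
- Spurious difference: p × (1 − s) × r

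Results:

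- Low end (p = 10%, s = 90%, r = 30%): 0.10 × 0.10 × 0.30 = 0.3 points.
- Middle (p = 30%, s = 70%, r = 50%): Masindi 0.30 × 0.70 = 21.0%; Hoima 0.30 × (0.70 + 0.15) = 25.5%; difference 4.5 points.
- High end (p = 40%, s = 60%, r = 70%): 0.40 × 0.40 × 0.70 = 11.2 points.
- A practice truly at 60% in both districts, s = 85%, r = 50%: 0.60 × 0.85 = 51.0% against 0.60 × (0.85 + 0.075) = 55.5%, a spurious 4.5-point benefit.

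Section 2.8 sizes the study for a 10-point difference with 609 mothers per group. With SE = √[(p_M(1 − p_M) + p_H(1 − p_H))/609] and no true effect, the middle morbidity case gives SE = √[(0.21 × 0.79 + 0.255 × 0.745)/609] = 0.0242 and z = 0.045/0.0242 = 1.86. A two-sided 5% test then rejects about 46% of the time. Over the whole morbidity range, rejection runs from about 5% to 99%. These rates ignore clustering. Allowing for it would lower them but leave the bias unchanged.

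**The case against.** The strongest reply is that Table 4 lists tools and does not say how they are combined. Section 2.11 gives outcomes to the SQ, and the notes to Table 3 separate a Hoima-only midterm review from the end-term comparison. The ttCR entries could therefore serve the midterm and process work alone, with a combining rule in a fuller document. That reading is possible, but neither Table 4 nor its notes states it. Followed literally, the table puts unequal sources into the comparison.

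Several stronger readings that a reader might infer are not supported:

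- *That the bias cannot be separated from a true effect.* The SQ is listed for all nine variables, so an SQ-only comparison remains available.
- *That maternal deaths in Masindi would be missed altogether.* Section 3.2 suggests that mothers are the usual respondents, but nothing restricts the SQ to them, and Table 4 lists the SQ for maternal death. At the national ratio of 336 per 100,000 live births given in the article, 609 mothers imply about 609 × 0.00336 ≈ 2 maternal deaths per group, too few for an informative comparison from any source.
- *That the spurious difference is about half the design effect.* The 4.5-point cases reflect chosen inputs and an either-source rule that the article does not state.
- *That the VHTR would settle the matter for deaths.* No section says it records deaths, and in Hoima it too is kept by the VHTs who deliver ttC.

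The article also has a safeguard in both districts. Section 2.4 requires ANC and child health cards or a mother-child passport, and section 3.2 plans to issue cards at first contact. This should improve SQ capture of card-recorded items such as ANC, though less so of minor illness or cord care.

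**Conclusion.** The point stands as an inconsistency with consequences. Table 4 gives Hoima an extra source, completed by those delivering the intervention, for six of nine variables, while section 2.11 reserves that source for process evaluation. As written, the end-term comparison is open to differential ascertainment, against ttC for events and in its favour for self-recorded practices.

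The size is unknown. About 0 to 11 percentage points is what the assumed capture rates produce under an either-source rule; it is not an estimate for this study. The conclusion rests on the ttCR being confined to Hoima (a strong inference) and on Table 4 governing the end-term comparison (its plain reading). For most variables the choice of source can still be corrected at analysis. How deaths are to be ascertained, including who answers for a mother who has died, needs settling before the end-term fieldwork.

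**What to change.** Reconcile Table 4 with section 2.11:

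1. State that every Hoima–Masindi comparison uses only sources available in both districts: the SQ, plus the VHTR for ANC uptake.
2. Keep the ttCR for process evaluation, the Hoima-only midterm review, or a sensitivity analysis labelled as such.
3. For deaths, use identical ascertainment in both districts, with the SQ answered by another household member when the mother has died. Add the VHTR only if the sponsor confirms that it records deaths in both districts.

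The cost is an edit to Table 4 and a respondent line in the questionnaire. The downside is that events recorded only in the ttCR no longer count in the main comparison, which matters most for rare events. Reporting them in the sensitivity analysis keeps them visible.

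### Table 4 defines birth weight only as 2.5 kg or more and names no analysis in kg; adding one alongside would recover much lost information if ttC shifts weight generally

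*Protocol article*

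**What the plan says.** Dependent variable 3 in Table 4 of the protocol article is described as "Appropriate birth weight of 2.5 kg or more". The study questionnaire is the only tool listed for it. Section 2.5 states the matching aim in the same form: to "ascertain the relationship between ttC implementation and appropriate pregnancy weight gain by end of pregnancy and appropriate birth weight".

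The only sizing is in section 2.8, for two proportions, "using an individual binary for a two-sided significant level α and power 1-β", with "α = 0.05 (two-sided), β = 0.2" and an anticipated difference of 10 percentage points. That difference is not tied to birth weight or to any other named outcome.

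Section 3 (Data Management and Analysis) assigns no model or scale to birth weight. It promises univariate, bivariate and multivariate analyses, checks of normality, and fixed or random effects models that allow for clustering.

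The article gives no reason for the cut and no birth-weight mean, SD, proportion below 2.5 kg, expected gain or intracluster correlation (ICC).

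**The concern.** Birth weight is one of five dependent variables and part of a named aim. Defining a dependent variable is the protocol's own task, and here the definition is a dichotomy.

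If most babies weigh well over 2.5 kg, the cut lies in the lower tail of the distribution. A moderate upward shift of the whole distribution then moves few babies across it. The study could report no clear difference in the proportion although weights had risen by an amount that the same babies' weights in kg would probably have shown. Some weight has to be obtained anyway before a baby can be classified against 2.5 kg.

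**Working it through.** **The plan's own figures.** The article states "This provided a 1107-sample size in the two districts" and then "This will be increased by 10% to 1218 participants to cater for a non-response". The second step reproduces: 1107 × 1.10 = 1217.7, rounded to 1218, or 609 per arm. The first does not follow from the stated inputs. A 10-point difference at two-sided 0.05 and 80% power needs at most 392 per arm (784 in total) at any baseline, so 1107 implies an unstated factor of at least 1107/784 = 1.41. That is a separate matter. For this point I take 609 per arm as given.

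**Assumptions, none of them in the documents.** Normal weights; SD 0.5 kg; control proportion below 2.5 kg of p₁ = 6% to 15%; the same gain for every baby. For clustering, ICC 0.02 with the article's cluster size of 60: 1 + 59 × 0.02 = 2.18, taken as 2.2, so effective n = 609/2.2 = 277 per arm.

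**Step 1: information kept by the cut.** For a small uniform shift, relative efficiency = φ(z_p)² / [p(1 − p)], where z_p is the standard normal quantile at p.

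| Below 2.5 kg | Efficiency | Information lost |
|---|---|---|
| 5% | 0.22 | 78% |
| 6% | 0.25 | 75% |
| 10% | 0.34 | 66% |
| 15% | 0.43 | 57% |
| 20% | 0.49 | 51% |

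**Step 2: power for a uniform gain of 0.10 kg.**

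- Cut: p₂ = Φ(Φ⁻¹(p₁) − gain/SD); power = Φ((p₁ − p₂)/√[(p₁q₁ + p₂q₂)/n] − 1.96), with q = 1 − p.
- Kg scale: power = Φ(gain/(SD√(2/n)) − 1.96).

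Example at p₁ = 10%, n = 609:

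- Cut: p₂ = Φ(−1.282 − 0.20) = 0.069; standard error 0.0159; z = 0.0308/0.0159 = 1.93; power 49%.
- Kg scale: standard error 0.5 × √(2/609) = 0.0287 kg; z = 0.10/0.0287 = 3.49; power 94%.

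| p₁ | Cut, no clustering | Kg, no clustering | Cut, design effect 2.2 | Kg, design effect 2.2 |
|---|---|---|---|---|
| 6% | 37% | 94% | 20% | 65% |
| 10% | 49% | 94% | 26% | 65% |
| 15% | 59% | 94% | 31% | 65% |

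**Step 3: other sizes of gain.**

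- 0.05 kg, no clustering: cut 13% to 20%, kg scale 41%.
- 0.15 kg, no clustering: cut 65% to 89%, kg scale above 99%.
- 0.15 kg, design effect 2.2: cut 35% to 58%, kg scale 94%.

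**Step 4: a different mechanism.** Let only babies below 2.5 kg gain weight, 0.2 kg each, with no clustering. The mean then rises by only 0.2 × p₁, while every baby between 2.3 and 2.5 kg crosses the cut.

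| p₁ | p₂ | Cut | Mean gain | Kg scale |
|---|---|---|---|---|
| 6% | 2.5% | 85% | 0.012 kg | 6% |
| 10% | 4.6% | 95% | 0.020 kg | 10% |
| 15% | 7.5% | 98% to 99% | 0.030 kg | 18% |

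The ranking of the two scales reverses.

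**The case against.** Several objections are sound.

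- **Exclusive use of the cut is not stated.** A reader might infer from Table 4 that birth weight will be analysed only as yes or no. The article does not say so: section 3 fixes no scale, and neither the full protocol nor any SAP is shown. What stands is narrower: the one outcome it defines is the dichotomy, and no analysis in kg is named.
- **A weight in kg is not confirmed.** No section says that the questionnaire records kilograms or copies them from a card. Section 2.4 requires mothers to hold cards or a passport, which makes it plausible, but section 3.2 expects some recall bias where cards are missing. Recalled or rounded weights would reduce the gain by an unknown amount. They would also misclassify babies near 2.5 kg, so they do not favour the cut.
- **A realistic effect need not be undetectable.** That stronger reading depends on an effect, SD and ICC that the documents do not supply. At 0.15 kg without clustering the cut has 65% to 89% power; at 0.05 kg both scales are weak. With clustering at 0.10 kg even the kg scale reaches only 65%, so the cut is not the sole cause of low power.
- **A general shift is itself an assumption.** The pregnancy visits in Table 1 cover danger signs, antenatal attendance, birth planning and facility delivery, which could act mainly on at-risk births. Step 4 shows that the mean would then perform far worse.
- **The stated aim concerns the proportion.** Section 2.5 asks about appropriate birth weight and Table 4 defines that at 2.5 kg. Replacing it with a mean would change the question.

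The last two objections defeat any proposal to demote the proportion. They do not count against adding the kg analysis beside it. Nor does either scale remove confounding from one purposively chosen district per arm; a more sensitive scale will also show existing district differences more readily.

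**Conclusion.** The point holds as a cheap improvement, not as an error that invalidates the outcome. The article defines birth weight only through the 2.5 kg cut. If ttC raises weights generally, that form loses 51% to 75% of the information for 6% to 20% of control babies below the cut. For a 0.10 kg gain and 6% to 15% below the cut, the kg scale adds 35 to 57 percentage points of power without clustering (94% against 37% to 59%). It adds 34 to 45 points with a design effect of 2.2 (65% against 20% to 31%).

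These sizes rest on normality, SD 0.5 kg, a uniform gain and usable weights in kg, none of which the documents establish. Because the likely mechanism is not known and the ranking depends on it, the sound course is to pre-specify both forms.

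**What to change.** 1. In Table 4, state that the questionnaire captures birth weight in kg, taken from the card where available, and records whether the value came from the card or from recall.
2. Keep the proportion at 2.5 kg or more as a formally analysed outcome, because it answers the aim in section 2.5.
3. In section 3, pre-specify beside it the adjusted mean difference in birth weight between districts, from the multilevel model already planned. Fix the choice of both forms before outcome data are seen, so that neither is selected on its result.

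This needs a line in Table 4 and one in section 3, with no extra women or visits. If the questionnaire does not yet hold a kg field, one field must be added. The downside is one additional pre-specified analysis, to be counted in any handling of multiplicity, and some noise from rounded or recalled weights.
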